#### Study population

Patients aged between 18 and 80 years old, within 1-week post-injury, and admitted to the hospital for moderate to severe TBI and/or mild TBI with neuroimaging abnormalities are eligible for inclusion (see Table 1). Additionally, individuals with orthopedic injury without TBI can participate as a control group if they meet the inclusion criteria outlined in Table 1 and do not meet any of the exclusion criteria.

**Table 1 tab1:** Eligibility criteria.

Inclusion Criteria for TBI Group A documented moderate to severe TBI posttraumatic Amnesia (PTA) > 24 h Loss of consciousness (LOC) >30 min Global cognitive score (GCS) <13, or Intracranial neuroimaging abnormalities (Head CT or MRI) Mild TBI with abnormalities on imaging exam. Ages 18–80 years-old 1 week post injury and admitted to the hospital for TBI. All participants must be fluent in English or Spanish. Inclusion Criteria for non-TBI Orthopedic Control Group: Abbreviated Injury Score of ≤4 (not life threatening) for extremity and/or pelvis injury and/or rib fracture Without evidence of TBI based on history or head CT 1 week post injury and admitted to the hospital for trauma. All participants must be fluent in English or Spanish. Exclusion Criteria for the study Significant polytrauma that would interfere with follow-up and outcome assessment. Major debilitating baseline mental health disorders, major debilitating neurological disease, impairing baseline awareness, cognition, or validity of follow-up and outcome assessment. Significant history of pre-existing conditions that would interfere with follow-up and outcome assessment (e.g., end-stage cancers). Patients on psychiatric hold. Prisoners or patients in custody, pregnancy, low likelihood of follow-up (e.g., participants or family indicating low interest, residence in another state or country, homelessness or lack of reliable contacts). Current participant in an interventional trial (e.g., drug, device, behavioral). Penetrating TBI, spinal cord injury with ASIA score of C or worse and contraindications to MRI.

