### Power and sample size

This study is powered to examine the relationship between the primary outcome of NIHTB_CB fluid composite score at 1-year postinjury and dynamic CA indices derived from frequency-domain analysis during the acute stage of TBI (i.e., <1-week postinjury). According to our previous study (13), the dynamic CA transfer function phase at low frequency range was positively correlated with NIHTB_CB fluid composite score (i.e., a higher phase, a better CA, was associated with better cognitive score), with the coefficient of determination (
$R^{2}$
) of 0.35 (or Pearson correlation coefficient = −0.593). Based on this information, it is estimated that 117 participants (i.e., a cohort of TBI *n* = 90 and orthopedic controls *n* = 27) will provide 82% power at a 5% two-sided significance level to detect a 0.053 increase in 
$R^{2}$
 attributed 2 additional dynamic CA variables (transfer function gain and coherence), adjusting for 6 confounding factors (initial GCS, posttraumatic amnesia, head CT scan, age, sex, and education) in a multiple regression model, where 
$R^{2}=$
0.35 when only the control factors are included in the model (NCSS PASS 16). With a 10% attrition rate, the total sample size of *n* = 130 participants (TBI = 100, control = 30) are required to be enrolled for this study.

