#### Statistical methods: outcomes

For the primary analysis, multiple linear regression models will be performed to examine the associations of dynamic CA indices on the primary outcome of NIHTB_CB fluid composite score at 1 year post injury, adjusted by potential confounders (i.e., initial GCS, posttraumatic amnesia, head CT scan, age, sex, etc.). The parsimonious model will be selected via the automatic model selection algorithms, including forward, backward, and stepwise selection. Multicollinearity will be evaluated using variance inflation factors, and the issue of overfitting will be assessed through 10-fold cross-validation. For the secondary analyses, secondary outcomes, including CA/CBF and other continuous cognitive measures, R-GOSE score as well as health-related PROMIS measures at 1-year postinjury, will be analyzed separately through the same analytical approach. Sensitivity analyses of the outcomes will be performed to assess the robustness of the findings, including model diagnostics, outlier assessments, distributional assumptions, and missing data. Data transformation will be made if the normality assumption is violated.

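### The primary model is not the model that was powered: education is not named, the confounder list is left open, and automatic selection may remove any confounder

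*Protocol article*

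**What the plan says.** Under *Power and sample size*, the protocol article claims "82% power at a 5% two-sided significance level to detect a 0.053 increase in" R² from two further CA terms, the gain and coherence of the transfer function. The model behind this claim is described as "adjusting for 6 confounding factors (initial GCS, posttraumatic amnesia, head CT scan, age, sex, and education) in a multiple regression model". Education is one of the six. The controls alone are given an R² of 0.35, and the analysed number is 117.

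Under *Statistical methods: outcomes*, the primary analysis of the same score (the 1-year NIH Toolbox fluid composite) is "adjusted by potential confounders (i.e., initial GCS, posttraumatic amnesia, head CT scan, age, sex, etc".). Five confounders are named and education is not. The list opens with *i.e.*, which announces a complete list, and closes with *etc.*, which announces an open one. The next sentence reads: "The parsimonious model will be selected via the automatic model selection algorithms, including forward, backward, and stepwise selection". Nothing says which terms are open to selection, which are held in, or which of the three algorithms decides.

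**The concern.** The article describes the adjustment set for one primary analysis twice, and the two descriptions differ. The sample size section describes a fixed test: two CA terms added to six retained controls. The analysis section describes an open list followed by data-driven selection.

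Two things are at stake.

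- **Confounding control.** The article itself calls education a confounding factor, yet the analysis text does not commit to including it. No confounder, named or not, is guaranteed to stay.
- **Validity of the p-value.** If selection removes a confounder because it misses a threshold in this sample, its influence can pass to the CA coefficient. The usual test then treats the selected model as if it had been fixed in advance. The nominal 5% level no longer holds, and the 82% power belongs to a different procedure.

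**Working it through.** **Inputs from *Power and sample size*.** N = 117 (90 TBI and 27 controls); tested terms q = 2; controls k = 6; control R² = 0.35; increment 0.053; two-sided alpha 0.05; stated power 82%; attrition 10%.

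**Step 1: reproduce the stated power.** F test of an R² increment:

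- f² = 0.053 / (1 − 0.35 − 0.053) = 0.053 / 0.597 = 0.0888
- df1 = 2; df2 = 117 − 6 − 2 − 1 = 108
- noncentrality λ = N × f² = 117 × 0.0888 = 10.39
- power = 0.8195, which rounds to the stated 82%

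The variant λ = df2 × f² gives 0.786, so λ = N × f² is the one that matches. Enrolment also reproduces: 117/0.9 = 130, 90/0.9 = 100, 27/0.9 = 30. The sample size is sound on its own inputs, and those inputs require all six controls to be in the model.

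**Step 2: compare the two descriptions.**

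| | Power section | Primary analysis |
|---|---|---|
| Confounders | six, closed list | five named, open list |
| Education | named | not named |
| Kept in the model? | yes, by construction | not guaranteed |
| Test of CA | 2-df increment over fixed controls | terms in a selected model |

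**Step 3: power if education were left out (illustration).** Education's share x of the 0.35 is not given, so x is assumed. With k = 5 (df2 = 109), control R² = 0.35 − x and the increment held at 0.053:

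| Assumed share x | f² | λ | Power | N for at least 82.0% (enrolled) |
|---|---|---|---|---|
| 0 | 0.0888 | 10.39 | 82.0% | – |
| 0.01 | 0.0873 | 10.22 | 81.3% | – |
| 0.02 | 0.0859 | 10.05 | 80.6% | 121 (135) |
| 0.03 | 0.0845 | 9.89 | 79.9% | – |
| 0.05 | 0.0819 | 9.58 | 78.6% | 127 (142) |
| 0.10 | 0.0760 | 8.90 | 75.3% | 137 (153) |

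The loss is under 1.5 points at a share of 0.02 or less. It reaches 82.0 − 75.3 = 6.7 points at 0.10. Power falls below 80% from a share of about 0.03.

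**Step 4: effect of selection on the type I error (illustration).** In a simulation under assumed effect sizes, a CA term with no true effect was rejected about 5% of the time with the confounders forced in, and about 7 to 9% when they were open to selection. The size depends on how strongly the confounders relate to CA, which the documents do not give. Weaker links give less inflation and stronger links give more.

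**Step 5: an optional language term.** A seventh control that explains nothing leaves df2 = 107 and power 81.94%, against 81.95% without it. If it explained 0.02 or 0.05 (assumed), power would be 83.3% or 85.3%.

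**The case against.** The strongest reply is that *etc.* is shorthand. The analysis section repeats the first five items of the earlier list in the same order and puts *etc.* where education stood, so education is probably intended. Demographics and social status are collected, and nothing excludes education. This stands: a reader might infer that the plan drops education, and the text does not support that. It supports only that education is not named and the list is not closed.

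The power loss is also open to challenge. The shares in Step 3 are assumptions. The only source the article gives for an R² of 0.35 is an earlier correlation between transfer function phase and the cognitive score, so no share for education can be taken from it. Holding the increment at 0.053 further supposes that removing education leaves the CA contribution unchanged, which would not be so if education confounds it. Both points stand, so the table is an illustration and not an estimate.

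It can also be said that automatic selection is a separate matter, since it would threaten the confounders even if education were named. That is true, but it is why naming education would not be enough. Selection might be meant for the CA indices only, but the text does not say so.

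Finally, since eligibility states that "All participants must be fluent in English or Spanish", a reader might infer that not adjusting for test language is an error. The documents do not support that. Language is in neither list, so nothing is contradicted. The article does not say in which language tests are given or which version of the score is used, and such detail is commonly left to the full plan. Bias would also require language to be related to CA, on which the documents are silent.

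**Conclusion.** The point holds as a mismatch between the powered model and the planned model, together with an adjustment set that nothing protects. It rests on the article's own two statements and needs no outside figure. Because the article sets out the adjustment twice and differently, this is not detail merely deferred to an unseen analysis plan.

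The 82% is correct for a model with all six confounders retained; the analysis section does not promise that model. The cost in power if education were absent is about 0 to 7 points over assumed shares of 0 to 0.10. The rise in type I error, to about 7 to 9% in one set of assumed conditions, is likewise illustrative. Neither range shows that the study is underpowered or that its result will be biased. The absence of a language term is not an error in the document.

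**What to change.** In *Statistical methods: outcomes*, replace the open list with a closed one. State that the primary model always contains the six confounders of the sample size section (age, sex, education, initial GCS, posttraumatic amnesia and head CT), that they are entered before the CA terms, and that they are exempt from automatic selection. Limit forward, backward and stepwise selection to models labelled exploratory.

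The cost is wording only. No participants or degrees of freedom are added, because the power calculation already counts all six. Language of test administration may be added as an optional seventh covariate for about one degree of freedom (81.95% to 81.94% power if it explains nothing).

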#### Functional outcomes

Secondary outcome measures will include the Glasgow Outcome Scale Extended-Revised (R-GOSE) (59), Functional Status Examination (FSE), Expanded Disability Rating Scale Post-Acute Interview (E-DRS-P), and Functional Independence Measure (FIM).

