### Statistical analysis plan

Discrete variables will be summarized using counts with percentages, and continuous variables using means with standard deviation or medians with interquartile ranges. The comparisons between TBI and OTC groups in dynamic CA indices during the acute phase will be evaluated using a two-sample t-test or nonparametric Wilcoxon test. No adjustment will be made for multiple comparisons, and therefore findings for secondary outcomes should be interpreted as exploratory. Two-sided 0.05 level of significance will be used for statistical hypothesis testing.

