#### Statistical analysis: additional analyses

Mixed-effects models with an unstructured covariance matrix will be used to estimate the primary outcome of brain volumes measured at 3 and 12 months postinjury; the models will include subjects as random effect and dynamic CA indices, time, and dynamic CA indices 
×
 time interaction as fixed-effects factors. Other covariates or potential confounders (e.g., age, sex, dynamic CA indices and others) will be included in these mixed-effects models. Conditional Akaike information criteria and other goodness of fit criteria will be applied to select the parsimonious mixed-effects model. Similar modeling and data analysis will be applied with DTI measure of white matter integrity as a dependent variable. In the secondary analysis, mediation models will be performed to study the overall association of Δ CA and CBF variables (both global CBF measured by 2D color-coded duplex ultrasonography and regional CBF measured by ASL) with the outcome of Δ NIHTB_CB fluid composite score and to estimate the extent to which this association is mediated by Δ brain volumes or white matter integrity. We will repeat the above procedures for the DMN connectivity from rs-fMRI to explore if the associations between cerebrovascular function recovery, cognitive and functional outcomes are mediated by changes in brain neural network connectivity. Secondary outcomes, including changes in cognitive outcomes, R-GOSE score and PROMIS measures, will be analyzed followed by similar analytical approaches, and evaluated both total effects of Δ CA/CBF variables and mediation effects of Δ brain volumes. No adjustments for multiple comparisons will be made for all secondary analyses, which are considered as exploratory analyses. Assumptions and diagnosis for mixed-effects models will be carefully evaluated. Missing data will be imputed using multiple imputation by chained equations and pattern mixture approaches as needed and evaluated by the sensitivity analyses.

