## Discussion

CAPCOG_TBI study is an observational study that will investigate long- term cognitive outcomes after msTBI at three level 1 trauma centers in Texas, USA. The main purpose of the study is to determine if acute cerebrovascular dysfunction after msTBI is associated with cognitive outcome at 1-year post-injury. To our knowledge, no prospective studies have evaluated cerebral vascular assessment in the acute phase and compared it with long-term cognitive outcomes in msTBI patients.

The rationale for the CAPCOG study arises from the significant variability in clinical outcomes and brain lesions resulting from trauma, which can range from no measurable impairment to a vegetative state (12, 61). This variability presents a considerable challenge in predicting and prognosticating cognitive outcomes following msTBI.

Previous studies have explored relationships between cerebrovascular dysfunction and cognitive outcomes at 6 and 12 months post-TBI (10, 62). However, these analyses were performed retrospectively. Unfortunately, the largest prospective studies published on this topic, analyzing long-term function outcomes, did not include cerebrovascular assessments (3, 11). Nonetheless, the acute cerebrovascular dysfunction assessed by CA in TBI may play a role in cognitive outcomes and prediction models. Therefore, this large longitudinal prospective study meets the urgent need to understand temporal associations of CA recovery with functional and cognitive recovery during the critical time window of 12 months after TBI.

Another point to raise is that the majority of studies assessing functional outcomes have relied exclusively on the GOSE, which is a crude measure of outcome. Robust use and the combination of more detailed cognitive assessments and functional scales are crucial for a comprehensive analysis of cognitive function outcomes, such as NIHTB-CB, RAVLT, WAIS-IV PSI, FIM, and PROMIS PROPr scales. To mitigate potential limitations in cognitive assessment, all of these scales will be employed in the CAPCOG_TBI study.

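### Twelve-month R-GOSE, an ordered-category secondary outcome, is assigned to linear regression with a normality-driven transformation; a proportional-odds model would suit it better

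*Protocol article*

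**What the plan says.** The Statistical methods: outcomes section of the protocol article sets out one outcome model: "For the primary analysis, multiple linear regression models will be performed to examine the associations of dynamic CA indices on the primary outcome", that outcome being the NIHTB_CB fluid composite score at 1 year. It then names R-GOSE among the secondary outcomes and states: "R-GOSE score as well as health-related PROMIS measures at 1-year postinjury, will be analyzed separately through the same analytical approach". The remedy for poor fit is a single sentence: "Data transformation will be made if the normality assumption is violated".

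Sensitivity analyses are planned, "including model diagnostics, outlier assessments, distributional assumptions, and missing data", but no alternative model for an ordered outcome is named there or anywhere else in the article. Where the authors want a distribution-free alternative they say so: the Statistical analysis plan section offers a Wilcoxon test beside the t-test for comparing CA indices between TBI and orthopedic controls.

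The Functional outcomes section and Table 2 list R-GOSE as a secondary outcome. On the standing of such outcomes the Statistical analysis plan section says: "No adjustment will be made for multiple comparisons, and therefore findings for secondary outcomes should be interpreted as exploratory".

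**The concern.** An outcome scale built from ordered categories has a direction but no defined distance between levels. Linear regression on the category codes supplies a distance anyway: each step counts as one unit, wherever on the scale it falls. The coefficient is then a mean change in category number per unit of the CA index, and its size depends on that coding.

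The planned fallback does not help. A transformation re-spaces the same few values. It leaves the ties in place, cannot make a variable with a handful of values normal, and substitutes a second arbitrary spacing for the first. If the decision to transform follows inspection of the residuals, the reported scale is also chosen after the data are seen.

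At stake is how readable the R-GOSE result will be. The Discussion notes that most studies of functional outcome have relied on the GOSE alone, so readers are likely to compare this result with earlier work. Bunching is plausible: the Discussion describes outcomes after trauma "which can range from no measurable impairment to a vegetative state", and the eligibility criteria also admit mild TBI with imaging abnormalities.

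**Working it through.** **1. The plan's own figure.** The Power and sample size section concerns the primary outcome only. Its inputs are N = 117, 2 tested variables, 6 controls, R² = 0.35 with controls, an R² increase of 0.053, and two-sided alpha 0.05.
- f² = 0.053 / (1 − 0.35 − 0.053) = 0.053 / 0.597 = 0.0888
- λ = N × f² = 10.39, with 2 and 117 − 2 − 6 − 1 = 108 degrees of freedom
- Power = 81.95%, against the stated 82%
- Attrition: 117 / 0.9 = 130

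The figure reproduces. No power is stated for R-GOSE, and changing the R-GOSE model alters none of these numbers.

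**2. What a transformation does to the steps.** The documents do not give the number of levels; assume eight, coded 1 to 8.

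| Coding | Step 1→2 | Step 7→8 | Ratio, bottom to top |
|---|---|---|---|
| Raw | 1 | 1 | 1 |
| Square root | 1.414 − 1 = 0.414 | 2.828 − 2.646 = 0.183 | 2.3 |
| Square | 4 − 1 = 3 | 64 − 49 = 15 | 0.2 |

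All three keep the same order. They disagree about the relative weight of the bottom and top steps, and nothing in the scale decides between them. A proportional-odds model uses the order only.

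**3. Operating characteristics.** These rest on simulation, with inputs that are assumptions and not in the documents.

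*Set-up A:* n = 100, eight levels with frequencies 15, 2, 8, 10, 15, 15, 20 and 15%, 300 replicates.
- Null: rejection 5.7% linear, 5.0% ordinal (Monte Carlo SE √(0.05 × 0.95 / 300) = 1.3 points).
- Log-odds 0.5 per SD of CA: power 77.7% linear, 80.0% ordinal (SE about 2.4 points each).

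*Set-up B:* n = 90, one CA index plus six covariates (log-odds 0.4 per SD each), CA log-odds 0.55 per SD, proportional odds true, 560–600 replicates per scenario, likelihood-ratio test for the ordinal model.

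| Assumed distribution | Type I, linear | Type I, ordinal | Power, linear | Power, ordinal | Power gain |
|---|---|---|---|---|---|
| Spread | 4.2% | 5.7% | 74.5% | 81.0% | 6.5 |
| Ceiling | 4.3% | 5.5% | 69.3% | 78.0% | 8.7 |
| Bimodal | 3.3% | 4.7% | 75.0% | 79.8% | 4.8 |

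The SE of the type I figures is about 0.9 points.

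A separate, smaller run of set-up B (400 replicates) used Wald tests for the ordinal model. Under the null it gave 6.0, 7.75 and 8.25% for ordinal against 5.75, 4.5 and 6.25% for linear. In the larger run the ordinal Wald test gave 4.7–5.5%. Linear regression shows no material inflation in any run. At this sample size the ordinal Wald test may run slightly above nominal, which favours the likelihood-ratio test.

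**4. Sparse categories.** A level with 2% frequency holds 0.02 × 90 = 1.8 of the 90 evaluable TBI participants; one with 1% holds 0.9. Some merging may be needed.

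**The case against.** The strongest reply is that little is lost. R-GOSE is one of several unranked secondary measures, the Discussion itself calls the GOSE crude, and secondary findings are declared exploratory. Linear regression holds its type I error. Many statisticians would accept an adjusted mean difference in such an outcome. The power gain in set-up B comes from data generated under proportional odds, which favours the ordinal model, and 1.2 to 1.5 points of difference in test size may explain part of it. Set-up A showed 80.0 − 77.7 = 2.3 points, within simulation error. All of this stands, and it sets the size of the point.

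A second reply is that this is a condensed article with distributional sensitivity analyses promised, so the alternative model may sit in a fuller plan. That carries less weight. The article does not leave the R-GOSE model open: it names the outcome, assigns it the linear approach and gives transformation as the remedy.

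A reader might infer more than the document supports:
- *That R-GOSE is the only global outcome covering the most impaired patients.* Table 2 lists FSE and E-DRS-P in both batteries as well.
- *That R-GOSE is the main functional result.* Nothing designates it so.
- *That the linear standard errors are invalid.* The simulations do not show this.
- *That deaths are miscoded.* The document does not say how deaths enter R-GOSE. Placing them in a category would be a new decision about what is estimated, not a correction.
- *That the change and mediation analyses must become ordinal too.* The additional analyses section does say: "Secondary outcomes, including changes in cognitive outcomes, R-GOSE score and PROMIS measures, will be analyzed followed by similar analytical approaches". But recasting a mediation decomposition for an ordinal model is a debatable redesign and does not follow from this point.

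**Conclusion.** The point holds as a modest improvement to one secondary analysis. The plan states a method that suits an ordered-category scale poorly, and its fallback does not cure the problem. The benefit is an estimate that does not depend on arbitrary category spacing, with possibly a few points of power (about 2 to 9 across the simulated set-ups). Neither set-up showed a power loss for the ordinal model.

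These sizes rest on eight levels, invented category frequencies, and proportional odds being true where set-up B was simulated. The primary analysis, the sample size of 130 and the stated 82% power are unaffected. There is no evidence of a false-positive problem with the linear model. It would also be too strong to say the change costs nothing, since the ordinal model brings its own assumption and its own difficulty with sparse levels.

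**What to change.** In Statistical methods: outcomes, take R-GOSE out of the sentence that applies the linear approach and out of the scope of the transformation sentence. Add wording to this effect:

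> R-GOSE at 1 year will be analysed by proportional-odds ordinal logistic regression, adjusted for the same confounders as the linear model. The common odds ratio per SD of the CA index will be reported with its 95% confidence interval and a likelihood-ratio test. The proportional-odds assumption will be checked, and adjacent sparse categories will be merged by a rule set before the data are analysed.

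Linear regression stays for the continuous outcomes. The way covariates are chosen need not change for this point, nor do the additional analyses.

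The cost is a short text change and standard software, with no extra participants or data. The small downside is the assumption check and possible merging of levels with only one or two people.
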